## Abstract

**Introduction::**

The treatment of abdominal aortic aneurysm (AAA) is increasingly performed via endovascular aneurysm repair (EVAR). Different types of fixation are possible with EVAR, i.e., below (infrarenal fixation) or above (suprarenal fixation) the renal arteries. Hemodynamic alterations in renal arterial flow with suprarenal (SR) fixation remain to be demonstrated. The IFIXEAR (Impact of Supra-renal Fixation of EVAR on Hemodynamics of Renal Arteries) study is designed to assess the hemodynamic effects at the ostia of at least 1 renal artery, generated immediately post-surgery by the implantation of an aortic stent with SR fixation.

**Methods::**

IFIXEAR is a prospective, 2 center study. Every patient undergoing elective EVAR with SR fixation is eligible for inclusion. Patients with previous hemodynamic disturbances to the ostia of 1 of the renal arteries are not eligible. All patients undergo echocardiography and renal arteries duplex ultrasound within a month before surgery, and at 1 and 12 months after surgery. The primary endpoint is hemodynamic disturbance, defined as a peak systolic velocity greater than 120 cm/second, at the ostia of 1 of the renal arteries in the immediate postoperative period.

**Ethics and dissemination::**

The study was approved by the Ethics Committee “Comité de Protection des Personnes Ouest V” under the number 18/019-2 on April 20, 2018. All patients provide written informed consent before inclusion. The University Hospital of Besancon is the trial sponsor. Results of the study will be submitted for publication in a peer-reviewed international medical journal.

**Registration::**

The trial is registered with ClinicalTrials.gov (Identifier: NCT03594786, principal investigator: [name], Registered on April 24, 2018).

## Introduction

1

Abdominal aortic aneurysm (AAA) affects 8% of men over 65 years of age. AAA rupture is fatal in more than 80% of cases. If detected early, prophylactic treatment, by either a surgical or endovascular approach, is recommended in France when the maximal transverse diameter exceeds 5 cm.^[1]^ Endovascular techniques are considered less invasive and are preferred in two thirds of cases.^[2,3]^ Endovascular aneurysm repair (EVAR) can be performed with infrarenal or suprarenal fixation (SR fixation). The choice depends the operators usual habits, the angulation ,and the length of the neck of the aneurysm.^[4]^

SR fixation presents at the level of its proximal part a bare metal stent, with in more than half of the cases, an interposition with regard to renal ostia.^[5,6]^ A hemodynamic impact is therefore possible at this level and likely to cause an alteration of renal vascularization. Animal studies have shown that SR fixation may compromise renal perfusion due to neointimal proliferation between the meshes of the uncovered stent, depending on the type of stent used.^[7,8]^ In addition, based on a computer simulation of patient-based data, Sun et al^[9]^ suggested a significant interference of SR fixation on renal arterial flow. They calculated that a single mesh of the covered stent centrally crossing the renal ostium could result in a flow reduction ranging from 21% to 29%, depending on the mesh size of the bare stent. However, in many studies, SR fixation has a worse effect in renal function. Elective EVAR is associated with a significant decline in estimated glomerular filtration rate (eGFR), and this effect is more pronounced with SR fixation.^[10,11]^ Nevertheless, the impact of SR fixation on renal artery function is not clearly defined.^[12]^ The development of renovascular disease, and possibly stenosis due to the stent crossing the renal ostia could explain this decline in renal function.

Currently, follow-up studies of EVAR are almost exclusively based on computed tomography angiography (CTA) scans.^[13]^ This exam does not appear suitable for assessing the renal hemodynamic impact of these patients.^[14]^ Duplex ultrasound is the only exam that can be used to perform hemodynamic analysis to detect flow disturbances in the renal arteries; and to appreciate the impact and the evolution of this disturbances and the stenosis.^[15]^ However, it is not used in this context for monitoring patients. In France, CTA scan is recommended at 1, 6, and 12 months after EVAR, and then every year thereafter, for follow-up.^[16]^ In the recent European recommendations, CTA scan is preferred at 1 month, the duplex ultrasound can be used in the follow-up then if the first CT scan is normal without endoleaks.^[4]^

Thus, the existence of hemodynamic alterations in renal arterial flow with SR fixation remains to be demonstrated.

## Objectives

2

The IFIXEAR (Impact of Supra-renal Fixation of EVAR on Hemodynamics of Renal Arteries) study aims to describe the hemodynamic disturbances to the ostia of the renal arteries generated immediately postsurgery by the implantation of an aortic stent with suprarenal fixation.

The secondary objectives are to quantify the hemodynamic disturbances at the ostia of the renal arteries generated by the implantation of an aortic stent with suprarenal fixation at 1 year; to assess the proportion of patients with renal artery stenosis at 1 year; to assess the proportion of poststenotic turbulence at 1 year; and to evaluate the course of glomerular filtration rate before and at 1 year after surgery.

## Methods and design

3

This manuscript is written in accordance with the SPIRIT guidelines.^[17]^

### Study design

3.1

IFIXEAR is a prospective, two-center study. Patients are being included at the University hospital of Besancon and the University Hospital Dijon-Bourgogne.

### Eligibility

3.2

Every patient undergoing EVAR with SR fixation is eligible for inclusion. Detailed inclusion and exclusion criteria for the present study are given below. Patients with ruptured AAA are not eligible for inclusion, because the management of the neck is different in emergency situations, and renal artery duplex ultrasound cannot be performed before the intervention.

### Inclusion criteria

3.3

1.Signed written informed consent2.Elective EVAR with suprarenal fixation3.Women must be postmenopausal for at least 24 months, or surgically sterilized, or for women of childbearing potential, use of an effective method of contraception.4.Affiliation to the French social security system, or beneficiary thereof.

### Exclusion criteria

3.4

1.Peak systolic velocity (PSV) > 120 cm/second2.Stenosis of at least 1 renal artery3.Dialysis4.Rupture of abdominal aortic aneurysm5.Renal stenting during the procedure6.Fenestrated EVAR7.Open surgery8.Legal incapacity or limited legal capacity9.Subject in the exclusion period of another study10.Pregnancy or lactation

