### Study outline

3.5

The eligibility criteria are verified during the preoperative consultation. The patient then receives information relating to the study by the surgeon and provides written informed consent for inclusion the day before the Duplex ultrasound.

Demographic data are collected. Patient characteristics, prior medical history, and preoperative creatinine levels are collected in the immediate preoperative period. Cardiovascular examination is performed. As part of this study, echocardiography to evaluate cardiac flow, and ultrasound of lower limbs and aorta are performed in the month before the intervention.

EVAR procedure is completed according to operator's usual habits without modification for the study.

At 1 month after EVAR, patients undergo CTA scan, provided renal function allows it, and a follow-up consultation with the surgeon. For the purposes of this study, patients will undergo (in addition to the recommended CTA scan) Doppler ultrasound of the renal arteries coupled with echocardiography to verify that renal artery hemodynamic changes are not secondary to modifications in cardiac output. Vascular exploration with ultrasound - Doppler will be performed by a single operator in each center, to guarantee better reproducibility and standardization of the examination. All ultrasound images taken for an examination will be recorded. Only hemodynamic impacts without a change in cardiac output will be attributed to suprarenal fixation of the stents.

At 1 year after EVAR, patients will undergo usual follow-up, and for the purposes of this study, will also undergo duplex ultrasound of the renal arteries and echocardiography. Creatinine levels will be recorded at 1 year.

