### Outcomes

3.6

The primary endpoint is significant hemodynamic disturbance in the immediate postoperative period, defined as peak systolic velocity (PSV) >120 cm/second at the ostia of at least 1 of the renal arteries, measured on duplex ultrasound at 1 month after intervention. The normal value of PSV is <120 cm/second in the renal artery.^[18]^ One examiner will perform the measurements in each center.

Secondary endpoints

1.Hemodynamic disturbances at 1 year, defined as a PSV > 120 cm/second at the ostia of at least 1 of the renal arteries.2.Stenosis of 1 of the renal arteries at 1 year defined by at least 1 of these criteria:PSV >180 cm/secondEnd-diastolic velocity (EDV) >50 cm/secondRenal-to-aortic ratio (RAR)>3.5 defined by relationship between PSV at the level of the lesion and the PSV of the interrenal aortaRenal-to-renal ratio (RRR)>3.3 defined by relationship between PSV at the level of the lesion and the PSV of the renal artery downstream of the lesionStenosis revealed by hemodynamic disturbance: disappearance of the “notch” (pre-systolic) or increase of the systolic rise time or reduction of the resistance index or poststenotic turbulenceMorphologic signs of stenosis: decrease in the size of a kidney compared to the contralateral kidney or in reference to a previous exam.3.One year hemodynamic repercussions on renal intra-parenchymal vascularization e.g., stenosis revealed by hemodynamic disturbance: disappearance of the “notch” (presystolic) or increase of the systolic rise time or reduction of the resistance index or poststenotic turbulence4.Course of estimated glomerular filtration rate (in ml/minute/1.73 m^2^) over time, calculated using the CKD-EPI formula.^[19]^

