### Statistical analysis

3.9

Quantitative variables will be described as mean ± standard deviation, or median [range] as appropriate. Qualitative variables will be described as number (percentage). The proportion of patients with hemodynamic disorders in the immediate postoperative period will be calculated with the associated 95% confidence interval. Preoperative and postoperative PSV variation as well as postoperative 1-year PSV variation associated with a 95% confidence interval will be calculated.

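### Crossing 120 cm/s after a baseline at or below 120 is attributed to the stent without a comparator or an allowance for measurement variability

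*Protocol article*

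**What the plan says.** All references are to the protocol article.

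- **Exclusion criteria (3.4):** the first criterion is "Peak systolic velocity (PSV) > 120 cm/second". The artery, the site and the number of readings are not given.
- **Outcomes (3.6):** the primary endpoint is a disturbance "defined as peak systolic velocity (PSV) >120 cm/second at the ostia of at least 1 of the renal arteries". The reading that counts is the one from the 1-month duplex examination. The first secondary endpoint applies the same cut-off at 1 year.
- **Abstract, Methods:** "All patients undergo echocardiography and renal arteries duplex ultrasound within a month before surgery, and at 1 and 12 months after surgery". This describes one preoperative renal examination. No repeat baseline, confirmatory reading or minimum rise is described.
- **Study design and Eligibility (3.1 to 3.3):** a two-centre cohort in which every patient has suprarenal fixation. No other group is described.
- **Objectives (2):** the aim is to describe disturbances "generated immediately postsurgery by the implantation of an aortic stent with suprarenal fixation".
- **Study outline (3.5):** a haemodynamic impact is attributed to suprarenal fixation only if cardiac output has not changed. One Doppler operator works in each centre and all images are recorded.
- **Statistical analysis (3.9):** one proportion with a 95% confidence interval, and "Preoperative and postoperative PSV variation as well as postoperative 1-year PSV variation associated with a 95% confidence interval will be calculated".

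**The concern.** With the exclusion and the endpoint set at the same value, the event rate at baseline is zero by construction. Every later reading above 120 cm/s is then a new event. Two arteries are examined and one is enough, which gives a noisy measurement two chances to cross.

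A new event has several possible sources: a true effect of the stent, other effects of the procedure or of time, a change in cardiac output, or ordinary variation between two examinations. The plan filters out only cardiac output and assigns the rest to the stent. Without a comparator or a repeatability margin, the reported proportion cannot separate a stent effect from measurement variability.

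The Introduction says that haemodynamic alterations with suprarenal fixation remain to be demonstrated. A proportion above zero would naturally be read as that demonstration, although some events are expected with an inert stent. The mean PSV change has a related problem: baselines are capped at 120 and follow-up values are not, so regression to the mean pushes the average change upward.

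**Working it through.** **1. The plan's own figure.** Sample size calculation (3.8) assumes a proportion of 20%, absolute precision of 10 points and alpha of 5%:

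n = 1.96² × 0.20 × 0.80 / 0.10² = 61.46, rounded up to 62.

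This reproduces the stated 62. The 70 to be included allow for 8/70 = 11.4% loss. The sample size is correct and is not affected by this point.

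**2. Inputs for the null calculation.** From the documents: exclusion above 120 cm/s; event if at least one artery is above 120 at follow-up; no comparator. The documents give no mean PSV, between-patient SD, left-right correlation or repeatability. The values below are assumptions and are therefore varied.

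**3. Simulation with no stent effect.** Each patient has two arteries with normally distributed true PSV T (correlation 0.5). Each examination reads T × (1 + CV × e), with e an independent standard normal error. Patients are kept if both baseline readings are at or below 120. The same T applies at follow-up.

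| Mean / SD / CV | Events, nobody excluded | Events, exclusion applied | Mean PSV change, cm/s | 95% CI for mean change wholly above 0 (n = 62) |
|---|---|---|---|---|
| 80 / 18 / 10% | 5.0% | 3.0% | +0.3 | about 5% of trials |
| 90 / 22 / 15% | 22% | 12.4% | +2.0 | about 22% |
| 100 / 18 / 15% | 33% | 20.2% | +3.3 | about 45% |

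The nominal value for the last column is 2.5%.

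**4. A second error model.** With additive error, a mean of 90, a between-patient SD of 15-20 and a within-patient SD of 10-15, chance events are about 5.5-12%. Over a wider grid (means 80-100, within-patient SD 0-20) they run from 0%, when there is no measurement variability, to about 28%.

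**5. Scale against the plan.** The plan anticipates at most 20%, known to within 10 points. With 62 patients and a chance rate of 3%, the probability of at least one event is 1 − 0.97⁶² = 85%; at 12% or more it is practically 100%.

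**6. Effect of requiring a rise from own baseline.** For the difference of two readings with the same CV, a 95% repeatability margin is 1.96 × √2 × CV of the baseline value:

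- CV 10%: 1.96 × 1.414 × 0.10 = 27.7%
- CV 15%: 1.96 × 1.414 × 0.15 = 41.6%

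Requiring both PSV above 120 and a rise beyond this margin in the same artery reduces chance events in the three scenarios from about 3-20% to about 0.7-5%.

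**The case against.** The strongest reply is that the study is descriptive. Its stated aim is to describe, the analysis is a proportion with a confidence interval, and there is no test and no reference rate. As description that is valid, and excluding prevalent cases with the outcome threshold is ordinary practice when incident events are counted. This stands. The difficulty lies in the causal wording of the Objectives and in the attribution rule of the Study outline, which go beyond description.

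The plan also has relevant safeguards: a single operator per centre, recorded images, echocardiography at each visit, and an analysis of PSV change beside the threshold. They reduce operator differences and address cardiac output. They leave within-operator and visit-to-visit variability in place, and the change analysis is itself uncontrolled.

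The size rests wholly on assumptions. The 20% corner needs a mean of 100 cm/s and a CV of 15%, where about 33% of candidates would already fail the baseline criterion. That sits uneasily with Outcomes, which gives values below 120 as normal. This stands too, so the range must be shown with its lower end.

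A reader might infer two stronger claims. The first is that truncation at 120 inflates the primary proportion. It does not: measurement variability causes the crossings, and the exclusion removes some of them (5.0% to 3.0%, 22% to 12.4%, 33% to 20.2%). The second is that a confidence interval for the PSV change above zero is bound to appear with no effect. It appears more often than it should, in about 5-45% of simulated trials, but not always.

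**Conclusion.** The point holds as a fault of attribution. If the plan is followed as written, crossings from measurement variability with stable cardiac output are counted as stent effects, and nothing in the design can separate the two.

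Under the stated assumptions this concerns about 3-20% of eligible patients, against a planned maximum of 20%; it approaches 0% if repeatability is very good. Regression to the mean bears on the PSV change only, with an upward bias of about 0.3 to 3.3 cm/s. None of these sizes is documented, because the article gives no PSV distribution or repeatability. The documents do not support calling the proportion invalid as a description, nor the sample size wrong.

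**What to change.** 1. **Attribution.** Report the overall proportion as descriptive. Reword the Objectives so that disturbances are those observed after implantation, and amend the rule in the Study outline so that a crossing without a cardiac-output change is not by itself attributed to the stent. Cost: wording only.

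2. **Rise from own baseline.** Pre-specify the proportion of patients with PSV above 120 cm/s and a rise from the same artery's own baseline beyond a stated repeatability margin, for example 1.96 × √2 × CV, with the CV justified and varied. The duplex data are already collected. Cost: one further analysis and a justified CV. Downside: the stricter definition may miss small true effects.

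3. **Exploratory contrast.** The Introduction reports "a bare metal stent, with in more than half of the cases, an interposition with regard to renal ostia", so some ostia should be uncrossed, though how many is unknown. Record from the 1-month CTA whether a bare strut crosses each ostium, and compare crossed with uncrossed ostia for PSV above 120 and for PSV change, adjusting for baseline PSV and allowing for clustering within patient. Cost: one field per artery and one model.

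   The contrast is non-randomised and will be missing for some patients, since "At 1 month after EVAR, patients undergo CTA scan, provided renal function allows it". Power is low: with 2 × 62 = 124 ostia split 68/56 (assumed) and treated as independent, 15% against 5% gives a standard error of √(0.15 × 0.85/68 + 0.05 × 0.95/56) = 0.052, an interval of about ±10 points and power of about 48%. It can support interpretation but should not carry the conclusion.

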### Study outline

3.5

The eligibility criteria are verified during the preoperative consultation. The patient then receives information relating to the study by the surgeon and provides written informed consent for inclusion the day before the Duplex ultrasound.

Demographic data are collected. Patient characteristics, prior medical history, and preoperative creatinine levels are collected in the immediate preoperative period. Cardiovascular examination is performed. As part of this study, echocardiography to evaluate cardiac flow, and ultrasound of lower limbs and aorta are performed in the month before the intervention.

EVAR procedure is completed according to operator's usual habits without modification for the study.

At 1 month after EVAR, patients undergo CTA scan, provided renal function allows it, and a follow-up consultation with the surgeon. For the purposes of this study, patients will undergo (in addition to the recommended CTA scan) Doppler ultrasound of the renal arteries coupled with echocardiography to verify that renal artery hemodynamic changes are not secondary to modifications in cardiac output. Vascular exploration with ultrasound - Doppler will be performed by a single operator in each center, to guarantee better reproducibility and standardization of the examination. All ultrasound images taken for an examination will be recorded. Only hemodynamic impacts without a change in cardiac output will be attributed to suprarenal fixation of the stents.

At 1 year after EVAR, patients will undergo usual follow-up, and for the purposes of this study, will also undergo duplex ultrasound of the renal arteries and echocardiography. Creatinine levels will be recorded at 1 year.

### Outcomes

3.6

The primary endpoint is significant hemodynamic disturbance in the immediate postoperative period, defined as peak systolic velocity (PSV) >120 cm/second at the ostia of at least 1 of the renal arteries, measured on duplex ultrasound at 1 month after intervention. The normal value of PSV is <120 cm/second in the renal artery.^[18]^ One examiner will perform the measurements in each center.

Secondary endpoints

1.Hemodynamic disturbances at 1 year, defined as a PSV > 120 cm/second at the ostia of at least 1 of the renal arteries.2.Stenosis of 1 of the renal arteries at 1 year defined by at least 1 of these criteria:PSV >180 cm/secondEnd-diastolic velocity (EDV) >50 cm/secondRenal-to-aortic ratio (RAR)>3.5 defined by relationship between PSV at the level of the lesion and the PSV of the interrenal aortaRenal-to-renal ratio (RRR)>3.3 defined by relationship between PSV at the level of the lesion and the PSV of the renal artery downstream of the lesionStenosis revealed by hemodynamic disturbance: disappearance of the “notch” (pre-systolic) or increase of the systolic rise time or reduction of the resistance index or poststenotic turbulenceMorphologic signs of stenosis: decrease in the size of a kidney compared to the contralateral kidney or in reference to a previous exam.3.One year hemodynamic repercussions on renal intra-parenchymal vascularization e.g., stenosis revealed by hemodynamic disturbance: disappearance of the “notch” (presystolic) or increase of the systolic rise time or reduction of the resistance index or poststenotic turbulence4.Course of estimated glomerular filtration rate (in ml/minute/1.73 m^2^) over time, calculated using the CKD-EPI formula.^[19]^

### Data management

3.7

Data will be managed using the Clean Web business application, an electronic clinical trial management solution from Telemedicine Technology. This solution meets the requirements of Good Clinical Practice, ICH, 21 CFR Part 11 (FDA) control and ensures secure data hosting. It also allows for a thorough implementation of users access rights based on their profile on the study.

### Sample size calculation

3.8

The main objective was to evaluate the proportion of patients with hemodynamic disturbances. We assume that the maximum proportion of these patients is 20%. At an alpha risk of 5%, with an absolute precision of 10%, the number of subjects required is 62. We will include 70 patients to take into account any patients who are lost to follow-up.^[20]^

